#### Flow cytometry to determine immune cell profiles

2.4.3.

Aliquots of PBMCs (100 μL) will be stained with appropriate antibodies for 30 min at room temperature in the dark in order to label, in separate samples, T lymphocytes, B lymphocytes, monocytes, NK cells, and granulocytes (Table 3). Then samples will be centrifuged at 300 *g* at 4°C for 5 min, the supernatant will be discarded, the pellet will be resuspended in 300 μL PBS, and the suspension will be measured using a FACSLyric ™ flow cytometer (BD Bioscience). The technician performing flow cytometry will be blinded to the origin of the samples.

**Table 3 tab3:** Antibody panels to identify immune cell subsets by flow cytometry.

Fluorophore	Antigen	Fluorophore	Antigen
T cell panel 1		T cell panel 2	
BV421	CD279	BV421	CD279
BV510	CD25	BV510	CD8
BV605	CD45	BV605	CD45
FITC	CCR7	FITC	CD38
PE	CD127	PE	CD69
PerCP-Cy5.5	CD3	PerCP-Cy5.5	CD3
PE-Cy7	CD28	PE-Cy7	CD28
APC	CD45RA	APC	CD45RO
APC-R700	FVS	APC-R700	FVS
APC-Cy7	CD4	APC-Cy7	CD4
B cell panel		Natural killer cell panel	
BV421	CD27	BV421	CD57
BV510	CD19	BV510	CD335
BV605	CD45	BV605	CD45
FITC	CD38	FITC	Lin(CD19/CD14/CD123/CD11C/FC)
PE	IgG	PE	CD127
PerCP-Cy5.5	IgM	PerCP-Cy5.5	CD3
PE-Cy7	CD274	PE-Cy7	CD56
APC	CD80	APC	CD314
APC-R700	FVS	APC-R700	FVS
APC-Cy7	IgD	APC-Cy7	CD16
Monocyte panel		Granulocyte panel	
BV421	CD284	BV421	CD123
BV510	CD40	BV510	CD15
BV605	CD45	BV605	CD45
FITC	CD14	FITC	CD14
PE	HLA-DR	PE	Siglec8
PerCP-Cy5.5	CD80	PerCP-Cy5.5	CD54
PE-Cy7	CD274	PE-Cy7	CD11b
APC	CD163	APC	CD181
APC-R700	FVS	APC-R700	FVS
APC-Cy7	CD16	APC-Cy7	CD64
		BV786	CD16

Flow cytometry data will be analyzed using FlowJo software (Treestar, Ashland, OR, United States), which will be gated to exclude debris, dead cells and doublets but retain single live cells for subsequent analysis. Immune cell subsets will be visualized in two dimensions map using t-distributed stochastic neighbor embedding (t-SNE) (34) and the “uniform manifold approximation and projection” algorithm (UMAP) (35). Then cells will be grouped into phenotypically homogeneous clusters using PhenoGraph (36) or FlowSOM (37), and the clusters will be characterized using Marker Enrichment Modeling (38).

#### Assay of cytokine levels in plasma

2.4.4.

Plasma samples will be analyzed for the following cytokines using commercial ELISAs: perforin, granzyme B, granulocyte-macrophage colony-stimulating factor, high mobility group box-1, heat shock protein-72, tumor necrosis factor-α, interferon-γ as well as interleukins (ILs)-1α, 1β, 2, 4, 6, 10, and 21, which will be measured according to the manufacturer’s instructions. Calibration curves will also be prepared according to the manufacturer’s instructions. Absorbance at appropriate wavelengths will be measured using a microplate reader (39).

#### Single-cell RNA sequencing

2.4.5.

Peripheral blood mononuclear cells will be prepared as described in section 2.4.2, and their viability will be assessed using trypan blue staining. When cell viability exceeds 85%, 5 × 10^4^ cells will be captured and used to construct libraries with the Chromium Next GEM Single Cell 5’ Reagent Kit (10x Genomics) according to the manufacturer’s instructions. The cells will be loaded into each channel, then partitioned into gel bead emulsions in the Chromium instrument, then followed as described (40).

### Statistical analysis

2.5.

Statistical analyses will be performed using Prism version 9 (GraphPad, San Diego, CA, United States). All statistical tests will be two-tailed, and results associated with *p* < 0.05 will be considered significant.

Continuous variables will be checked for normal distribution using the Shapiro–Wilk test and D’Agostino-Pearson omnibus normality test. If normally distributed, continuous data will be reported as mean (SD), and inter-cohort differences will be assessed for significance using one-way ANOVA or Student’s *t*-test. If skewed, continuous data will be reported as median (range or interquartile range), and inter-cohort differences and multiple pairwise comparisons will be assessed using a non-parametric Kruskal Wallis test or Mann–Whitney test.

Categorical variables will be reported as the number of cases (percentage). Inter-cohort differences in such variables will be assessed using the Chi-squared test or Fisher’s exact test. Inter-cohort differences in ordinal variables will be assessed using the Kruskal Wallis test or Mann–Whitney test comparisons.

Subgroup analyses will be performed according to the type of heatstroke (CHS or EHS). CHS always results from passive exposure to high ambient temperature, often accompanied by high humidity. EHS, in contrast, occurs in young individuals during vigorous exercise in hot or temperate environments (1).

Student’s *t*-test or Mann–Whitney test will be used to detect correlations between specific immune cell subsets and prognosis of heatstroke patients. The ability of such subsets to predict heatstroke and prognosis of affected individuals will be assessed using receiver operating characteristic curves, based on optimal thresholds obtained by maximizing the Youden index. Sensitivity, specificity, predictive values, and likelihood ratios will be calculated.

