#### Participant matching

2.1.2.

Heatstroke patients will be matched 1:1 with sepsis patients, CPB patients and healthy controls using propensity score analysis based on nearest-neighbor matching and a caliper width of 0.2 of the standard deviation of the logit of the propensity score (20). Covariates during matching of heatstroke and sepsis patients will be sex, age, body weight, Sequential Organ Failure Assessment (SOFA) score (21), comorbidities, and treatment history. Covariates during matching of heatstroke and CPB patients will be sex, age, body weight, comorbidities, and treatment history. Covariates during matching of heatstroke patients and healthy controls will be sex, age, and body weight.

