### Endpoints

2.2.

The aims of this case–control study are to identify the diagnostic immune cells biomarker(s) of heatstroke and prognostic immune cells biomarker(s) of heatstroke within 30 days.

For exploring diagnostic biomarker(s) that distinguishes patients with heatstroke from patients with sepsis, patients with aseptic inflammation and healthy individuals, because this trial is a case–control study, no endpoints can be provided.

For exploring prognostic biomarker(s) for patients with heatstroke, the primary endpoint is all-cause mortality within 30 days. The secondary endpoints include incidence of the organ injury events within 30 days, including neurological dysfunction, acute heart failure, acute renal failure, or respiratory failure, which are diagnosed as following:

Neurological dysfunction will include stroke, which will be diagnosed based on symptoms of unconsciousness or focal neurologic deficit and the results of computerized tomography and magnetic resonance imaging; and delirium, which will be diagnosed as described (22).

Acute heart failure will be diagnosed according to symptoms of breathlessness, tiredness, and fatigue; clinical signs; abnormalities of electrocardiogram(ECG) such as atrial fibrillation, Q waves, left ventricle hypertrophy, and a widened QRS complex (23); left ventricular ejection fraction (LVEF) ≤ 40% based on the results of echocardiography (23); and elevated levels of B-type natriuretic peptide (BNP) or NT-proBNP (24).

Acute renal failure will be defined as stage 3 acute kidney injury according to the KDIGO criteria (25): stage3: creatinine level in serum ≥4.0 mg/dL (353.60 μmol/L) or ≥ 3 times baseline within 7 days, or requirement for renal replacement therapy, or urine output <0.3 mL/kg/h for ≥24 h OR anuria for ≥12 h.

Respiratory failure will be defined as pH < 7.35 and PaCO_2_ > 45 mmHg or as PaO_2_/FiO_2_ < 200 based on invasive or non-invasive ventilation or arterial blood gas analysis (26, 27) within 30 days. If patients with concomitant pulmonary diseases prior to admission meet above diagnostic criteria, the patient will not be considered to have lung injury caused by heatstroke and will be excluded.

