### Minimal sample size

2.3.

We did not calculate minimal sample size to achieve a given statistical power because this is an exploratory study (28, 29) and we are unaware of other studies with a similar design and purpose. Recent studies of the protective effects of precooling and curcumin on organ injury among patients with EHS included only 8–12 participants (30, 31). A study that examined immune cell dynamics during EHS was able to obtain statistically significant results using only 11 patients (32). Therefore, to differentiate the immune profiles, we aim to enroll at least 40 subjects in each of the four cohorts.

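### The prognostic analysis is unadjusted throughout, so it cannot show whether an immune cell subset adds anything to SOFA or age

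*Protocol article*

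**What the plan says.** Section 2.2 sets the outcome for the prognostic question: "the primary endpoint is all-cause mortality within 30 days". Organ injury events within 30 days are secondary.

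Section 2.5 names two analyses for it. The first is a two-group comparison: Student's t-test or "Mann–Whitney test will be used to detect correlations between specific immune cell subsets and prognosis of heatstroke patients". The second is discrimination: "The ability of such subsets to predict heatstroke and prognosis of affected individuals will be assessed using receiver operating characteristic curves", with thresholds that maximise the Youden index. The general rule in the same section is two-tailed testing at p < 0.05. No regression, covariate or comparison with an existing score is named. The only stratification is by classic versus exertional heatstroke.

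Two obvious covariates are within reach. Section 2.4 records age at baseline for everyone. Section 2.1.2 matches heatstroke to sepsis patients on "sex, age, body weight, Sequential Organ Failure Assessment (SOFA) score (21), comorbidities, and treatment history", so SOFA has to be obtained for heatstroke patients. The article does not say when it is scored, and Table 2 does not list it.

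On size, section 2.3 states: "we aim to enroll at least 40 subjects in each of the four cohorts". It gives no power calculation.

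**The concern.** Matching balances heatstroke patients against the other cohorts. Inside the heatstroke cohort, those who die may well differ from survivors in organ dysfunction and age, and nothing in the plan deals with that. The article's own introduction links excessive inflammation to multi-organ failure and death, and blood is drawn within 24 h after admission, when organ injury may already be present. A subset can therefore differ between deaths and survivors only because it moves with severity.

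At stake is what a positive result would mean. The discussion hopes to identify high-risk patients and to lay foundations for immunotherapy. If the subset repeats what SOFA and age already show, it serves neither purpose well, and the planned output would not reveal this. The ROC step does not help, because a severity proxy also has an AUC above 0.5.

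**Working it through.** **The plan's own figure.** The target of 40 per cohort cannot be reproduced. Section 2.3 gives no effect size, SD, event rate or power, and cites only earlier studies of 8–12 and 11 patients.

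**Inputs from the article.** n = 40 heatstroke patients (section 2.3); two-sided alpha 0.05 (section 2.5); mortality 30–60% (introduction, given as how high rates can be, so background and not a planning rate).

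**Inputs assumed, not in the article.** Marker–SOFA correlation ρ = 0, 0.3, 0.5, 0.7; odds ratio for death per SD of SOFA = 2, 3, 4.

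**Step 1: group sizes.** Deaths = 40 × 0.30 = 12 to 40 × 0.60 = 24. The smaller outcome group is 12 at 30% mortality, at most 20 (at 50%), and 40 − 24 = 16 survivors at 60%. A three-term model (marker, SOFA, age) has 12/3 = 4 to 20/3 ≈ 7 patients per term in that group; a two-term model has 12/2 = 6 to 20/2 = 10.

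**Step 2: detectable difference.** At 80% power, d = (1.960 + 0.842) × √(1/deaths + 1/survivors):
- 12 and 28: 2.802 × 0.345 = 0.97 SD
- 18 and 22: 2.802 × 0.318 = 0.89 SD
- 24 and 16: 2.802 × 0.323 = 0.90 SD

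**Step 3: simulation.** Severity S ~ N(0,1), measured perfectly by SOFA. Death follows logit P = a + ln(OR) × S, with a set to give 30, 45 or 60% mortality. Marker = ρS + √(1 − ρ²) × noise, so it has no effect on death given S. There were 2,000 studies of 40 patients per setting. The planned Mann–Whitney test was compared with two SOFA-adjusted tests. The table shows the percentage of studies with p < 0.05.

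| ρ | Mann–Whitney, all settings | Mann–Whitney, 45% mortality, OR 3 | SOFA-adjusted linear model | SOFA-adjusted logistic LR test | Mean marker AUC |
|---|---|---|---|---|---|
| 0 | 3.9–5.7 | 5.4 | 4.3–5.5 | 5.3–7.0 | 0.50 |
| 0.3 | 7.7–13.9 | 11.7 | 4.1–5.3 | 5.1–6.8 | 0.55–0.59 |
| 0.5 | 13.5–35.4 | 27.0 | 4.2–5.5 | 5.2–7.4 | 0.59–0.65 |
| 0.7 | 22.3–61.1 | 48.5 | 4.0–5.6 | 5.1–6.9 | 0.62–0.71 |

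The likelihood-ratio test runs slightly above 5% because the sample is small.

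**Step 4: what adjustment costs.** At ρ = 0.7 the variance inflation is 1/(1 − 0.7²) = 1/0.51 = 1.96, and √1.96 = 1.40, so intervals are about 40% wider.

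**Step 5: if SOFA measures severity imperfectly.** With an assumed reliability of 0.6, ρ = 0.7 and OR 4, the adjusted linear model still flags the marker in about 18–21% of studies. Adjustment reduces the problem and does not abolish it.

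**The case against.** The strongest reply is that the article asks a different question. It wants markers that predict prognosis and nowhere requires them to be independent of severity. A marker with a true AUC of 0.62–0.71 for death is prognostic, and finding it significant is a correct answer to the hypothesis tested. This stands. A reader might take the 8–61% as a false-positive rate, or infer that severity proxies will inevitably be declared prognostic. The documents support neither: the unadjusted and adjusted tests address different null hypotheses, and the rates depend on correlations and a SOFA effect that the article does not give.

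A reader might also infer that a SOFA-adjusted model should replace the planned analysis. That is not supported either. On the introduction's account, inflammation leads to organ failure, so SOFA may partly mediate the immune effect, and adjusting for it could remove some of the signal sought. The number of deaths is not secured: Table 1 admits patients with either high core temperature or CNS symptoms, and if mortality were 10–20% (an assumption) there would be 40 × 0.10 = 4 to 40 × 0.20 = 8 deaths.

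That SOFA is available at admission is an inference from the matching covariates. The classic/exertional subgroups do separate age in part, since the article describes exertional cases as young, but they do not address severity and they split a cohort of about 40.

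Two defences do not stand. The exploratory label does not answer the point, because section 2.5 still applies a significance rule and reports cut-offs and predictive values. An unseen analysis plan does not answer it either, because the point concerns the method the article names, not omitted detail.

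**Conclusion.** The point holds as a limit on what the study can conclude. As written, section 2.5 can establish unadjusted association and discrimination, and cannot show whether a subset adds to SOFA or age. A marker with no effect given SOFA would be significant in roughly 8–14%, 14–35% or 22–61% of studies at correlations of 0.3, 0.5 and 0.7.

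Those figures rest on 40 patients, 30–60% mortality, a SOFA odds ratio of 2–4 per SD, and SOFA measuring severity without error. The direction is the same at every non-zero correlation tried; the size is uncertain. With only differences of about 0.9–1.0 SD detectable at 80% power, a severity proxy will often be missed as well as often flagged. An additional analysis is warranted, not a replacement of the planned one.

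**What to change.** 1. Keep the t-test or Mann–Whitney tests and the ROC curves, labelled as the unadjusted analysis.
2. State that SOFA is scored at the time of blood sampling (within 24 h of admission) and recorded for all heatstroke patients, and add it to Table 2.
3. Add a pre-specified Firth-penalised logistic regression of 30-day death on marker plus SOFA, with age only if the smaller outcome group allows. Report the adjusted odds ratio with its confidence interval, and the AUC gain over SOFA alone.
4. Where this model does not support added value, limit the conclusion to unadjusted association.
5. Say in advance that the adjusted estimate will be read knowing that SOFA may partly mediate immune effects.
6. Do not carry the model unchanged to the organ-injury endpoints, because renal, respiratory, cardiac and neurological failure overlap with what SOFA scores.

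No new patients, samples or visits are needed. The costs are a statistical package other than Prism, a SOFA entry on the case report form, wider intervals, and a model that may be unstable if deaths are few.

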## Introduction

1.

Heatstroke, which can be categorized as classic heatstroke (CHS) or exertional heatstroke (EHS) depending on its cause (1), is the most life-threatening form of hyperthermia (>40.5°C), and it involves central nervous system dysfunction and multi-organ failure (2). Even with intensive care, mortality rates of heatstroke patients can be as high as 30–60% (1, 2). The incidence of heatstroke-related deaths has been increasing globally during the past 2 decades, as record-breaking heatwaves have occurred (1). Heatstroke survivors may experience long-term neurological and cardiovascular complications (1, 2).

Hyperthermia can damage proteins, lipids, and nucleic acids, as well as kill cells directly (3, 4), inducing the production of cytokines to protect against tissue injury (5, 6). If thermoregulation fails to maintain core temperature within an appropriate range, inflammatory responses may become excessive and injure tissue, leading to multi-organ failure and death (7–9), akin to systemic inflammatory response syndrome (SIRS) (10–15). In addition, heatstroke can compromise gastrointestinal integrity, allowing endotoxins and pathogens to enter the circulation and trigger endotoxemia (14). However, potentially informative differences in immune profiles among patients with heatstroke, SIRS, or sepsis have not been fully elucidated.

For lack of a specific biomarker (1), heatstroke is diagnosed based on hyperthermia, history of exposure to extreme heat or vigorous exertion, and alterations of the central nervous system (6, 7). Researchers have undertaken genomic, epigenomic, transcriptomic, proteomic, and metabolomic studies in an effort to identify diagnostic biomarkers (16–18), without much success. The rate of false positive diagnosis of heatstroke remains as high as 24% and the rate of false negative diagnosis as high as 64.5%, especially among patients with atypical symptoms (2). To make matters worse, heatstroke can be difficult to differentiate from sepsis, especially when it involves leukocytosis, which can delay cooling treatments that substantially improve prognosis (1).

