#### Inclusion and exclusion criteria

2.1.1.

Participants will be recruited from the International Medical Center and from the Departments of Emergency Medicine and of Anesthesiology at West China Hospital of Sichuan University. Four cohorts of 40 individuals each will be recruited: heatstroke patients, sepsis patients, patients undergoing CPB, and healthy controls. The inclusion and exclusion criteria for each cohort are shown in Table 1. Participant recruitment and data collection will begin on January 1, 2023 and will continue until October 31, 2023.

**Table 1 tab1:** Inclusion and exclusion criteria for subject enrollment.

Subjects	Inclusion criteria	Exclusion criteria
Heatstroke patients	(1) Age ≥ 18 years	(1) Pregnant women.
	(2) History of exposure to extreme environmental heat or vigorous muscle exertion	
	(3) Core body temperature > 40°C or symptoms of central nervous system (CNS) dysfunction, such as coma, delirium, or convulsions	(2) Comorbid with immune system disease within the 6 months prior to admission, including but not limited to acquired immune deficiency syndrome (AIDS), multiple myeloma, rheumatoid arthritis, systemic lupus erythematosus, multiple sclerosis, myasthenia gravis, scleroderma, Crohn’s disease, and ulcerative colitis.
	(4) Written informed consent to participate	
Sepsis patients	(1) Age ≥ 18 years	(3) Comorbid with malignant tumor and hematological diseases.
	(2) Suspected or known infection	
	(3) Sequential organ failure assessment (SOFA) score ≥ 2	
	(4) Written informed consent to participate	(4) History of organ or bone marrow transplantation.
Patients undergoing CPB	(1) Age ≥ 18 years	
	(2) Valve replacement or coronary artery bypass under cardiopulmonary bypass	
	(3) Written informed consent to participate	
Healthy controls	(1) Age ≥ 18 years	(5) History of immunosuppressive therapy, including glucocorticoids, soluble microbial products (SMSs), polyclonal and monoclonal antibodies, antimetabolite and alkylating agents, or radiotherapy within the 6 months prior to admission.
	(2) Body mass index 18–24 kg/m^2^	
	(3) Health examination within the previous 6 months indicated no abnormality	
	(4) Written informed consent to participate	

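### The prognostic comparison relies on Student's t-test with no allowance for unequal spread, although deaths and survivors will probably differ in number; Welch's versions hold the 5% level at little cost

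*Protocol article*

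**What the plan says.** Section 2.5 (Statistical analysis) of the protocol article sets the rule: "All statistical tests will be two-tailed, and results associated with" p below 0.05 count as significant. Continuous variables are checked for normality with two named tests, and the result decides the method.

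- Normal data between cohorts: "inter-cohort differences will be assessed for significance using one-way ANOVA or" Student's t-test.
- Skewed data between cohorts: "inter-cohort differences and multiple pairwise comparisons will be assessed using a non-parametric Kruskal Wallis test or" the Mann–Whitney test.
- Prognosis within the heatstroke cohort: Student's t-test or the Mann–Whitney test "will be used to detect correlations between specific immune cell subsets and prognosis of heatstroke patients".

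No unequal-variance version is named, and no step looks at spread.

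On group sizes, section 2.1.1 states: "Four cohorts of 40 individuals each will be recruited". Section 2.3 says "we aim to enroll at least 40 subjects in each of the four cohorts", and section 2.1.2 matches heatstroke patients 1:1 to each other cohort. Section 2.2 makes 30-day all-cause mortality the primary prognostic endpoint. The article does not forecast the number of deaths. Its only guide is the Introduction, which says that "mortality rates of heatstroke patients can be as high as 30–60" per cent.

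**The concern.** Student's t-test pools the two sample variances. With equal group sizes, this does little harm when the true variances differ. With unequal sizes, the pooled estimate is dominated by the larger group, and the standard error of the difference is then too small or too large. If the smaller group is the more variable one, false positives exceed 5%; if it is the less variable one, the test becomes conservative.

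The between-cohort comparisons are planned with equal sizes. The prognostic comparison is different, because outcome forms its groups. Prognosis is one of the study's two stated aims, so the comparison most exposed to the problem is a central one. Readers of the results could not correct for it, because the direction of the error depends on spreads that are unknown at the planning stage. A normality check does not detect unequal spread.

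**Working it through.** **Inputs from the protocol article.** Two-sided 0.05 per test (section 2.5); 40 per cohort (sections 2.1.1 and 2.3); background mortality 30–60% (Introduction). Applied to 40 patients: 0.30 × 40 = 12 deaths v 28 survivors, and 0.60 × 40 = 24 v 16.

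**Assumptions.** The article gives no SDs, so SD ratios (deaths to survivors) of 0.5, 1, 1.5 and 2 are assumed. Data are normal, since that is the branch in which Student's t is used.

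**Formulas.** Student: t = (m1 − m2) / √[sp²(1/n1 + 1/n2)], with sp² = [(n1 − 1)s1² + (n2 − 1)s2²] / (n1 + n2 − 2). Welch: t = (m1 − m2) / √(s1²/n1 + s2²/n2), with Satterthwaite degrees of freedom.

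**Mechanism, with the survivors' SD set to 1.** Compare the variance of the difference that Student's t assumes on average with the true one.

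- 12 v 28, ratio 2: sp² = (11×4 + 27×1)/38 = 1.868. Assumed variance 1.868 × (1/12 + 1/28) = 0.222; true variance 4/12 + 1/28 = 0.369. The standard error is √(0.222/0.369) = 0.78 of what it should be.
- 12 v 28, ratio 0.5: sp² = (11×0.25 + 27)/38 = 0.783. Assumed 0.0932; true 0.25/12 + 1/28 = 0.0565. The standard error is 1.28 times too large.
- 24 v 16, ratio 2: sp² = (23×4 + 15)/38 = 2.816. Assumed 0.293; true 4/24 + 1/16 = 0.229. The standard error is 1.13 times too large.
- 20 v 20, ratio 2: sp² = 2.5. Assumed 0.25; true 4/20 + 1/20 = 0.25. No distortion.

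**Check of the nominal level.** There is no power calculation in the article to reproduce. In simulations under the null (100,000 replicates per t-test setting, 50,000 per ANOVA setting), equal spreads return 4.9–5.1% for Student's t at the splits tabulated below and 4.9% for ANOVA with four groups of 40.

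**Type I error of Student's t, deaths v survivors:**

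| Split | Ratio 0.5 | Ratio 1 | Ratio 1.5 | Ratio 2 | Welch, all four ratios |
|---|---|---|---|---|---|
| 12 v 28 | 1.4% | 5.0% | 9.5% | 12.9% | 4.9–5.2% |
| 16 v 24 | 2.8% | 4.9% | 7.0% | 8.5% | 4.8–5.0% |
| 20 v 20 | 5.4% | 5.0% | 5.2% | 5.2% | 4.9–5.1% |
| 24 v 16 | 8.6% | 5.1% | 3.7% | 2.9% | 4.8–5.1% |

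Fewer deaths widen the range. At 8 v 32, Student's t runs from 0.6% (ratio 0.5) to 18.3% (ratio 2).

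**Cohort against cohort, 40 v 40.** Student's t gives 4.9%, 5.0%, 5.1%, 5.3% and 5.4% at SD ratios 1, 1.5, 2, 3 and 5.

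**One-way ANOVA, four cohorts of 40.** SDs 2,2,2,1 give 5.4%; 2,2,1.5,1 give 5.8%; 3,3,3,1 give 6.0%; 3,3,2,1 give 6.1%; 3,1,1,1 give 8.3%. Welch's ANOVA gives 4.9–5.2% throughout.

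**Power when spreads are in fact equal, true difference 1 SD.** 12 v 28: Student 80.5%, Welch 78.6%. 16 v 24: 85.3% v 84.9%. For 40 v 40 at 0.64 SD: 80.7% v 80.6%.

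**The case against.** The strongest objection is that the distortion is conditional throughout. The article gives no SDs and no expected number of deaths. Its mortality figure is an upper background range, not a forecast for this cohort, and within that range a 20 v 20 split would leave Student's t intact. Student's t also applies only when the normality checks pass; otherwise the Mann–Whitney test is used. All of this stands, and it is why the claim is that the error rate can depart from 5%, not that it will.

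It can also be said that the choice of t-test variant belongs in an analysis plan that is not shown. That carries less weight here. The article names the test and states the criterion for switching, so the method is stated rather than left open.

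Three stronger readings are tempting, and the document does not support them.

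- A reader might infer that unequal sizes or unequal spreads alone spoil Student's t, so that sick-against-healthy comparisons are wrong too. Both must differ. At the planned 40 v 40 the test stays at 5.4% or below even with a five-fold SD ratio.
- A reader might infer that pairwise cohort contrasts after ANOVA are badly off because they share one pooled variance across all four cohorts. Section 2.5 names no such procedure. For normal data it names ANOVA or a t-test, and a t-test uses only its own two groups.
- A reader might infer that classic and exertional heatstroke will be compared with each other by Student's t-test. Section 2.5 announces subgroup analyses by type but gives neither that test nor the subgroup sizes.

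**Conclusion.** The point holds in a limited form. For prognosis, section 2.5 names an equal-variance test and has no provision for unequal spread, in a comparison whose group sizes will probably differ. Under assumed SD ratios of 0.5 to 2, the type I error of Student's t lies between 1.4% and 12.9% at 12 v 28, between 2.8% and 8.5% at 16 v 24, and between 2.9% and 8.6% at 24 v 16. The direction reverses once deaths become the larger group. Welch's t stays near 5% in all of these settings. The two-sample comparisons between cohorts of 40 are essentially sound as planned. The four-group ANOVA is mildly liberal under unequal spreads, and reaches 8.3% only when one cohort alone has three times the SD of the rest.

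These figures rest on normal data, on the assumed SD ratios, and on carrying the background mortality over to 40 patients. In an exploratory study without a power calculation the consequence is modest, so this is a desirable improvement and not a serious defect.

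**What to change.** In section 2.5, replace Student's t-test with Welch's t-test for the prognostic comparisons and for any other comparison of groups of unequal size. Replace one-way ANOVA with Welch's ANOVA across cohorts and, if pairwise comparisons follow it, use unequal-variance versions. Make these the default, not a fallback after a variance test.

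The cost is wording only, plus up to about 2 percentage points of power when variances are in fact equal (80.5% v 78.6% at 12 v 28). Welch's t is not exact with very few deaths: at 4 v 36 it rejects 5.5–6.2% of the time. Results based on so few deaths should be read with caution whichever test is used.

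### Cut-offs are chosen by maximum Youden index and judged in the same patients, so the planned accuracy figures are biased upward, most of all for prognosis

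*Protocol article*

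**What the plan says.** Section 2.5 compares immune cell subsets between heatstroke patients with different prognosis by a t-test or Mann–Whitney test. Tests are two-sided, and results with p below 0.05 "will be considered significant". The next sentence refers back to those subsets and assesses by ROC curves how well they predict heatstroke and its prognosis, "based on optimal thresholds obtained by maximizing the Youden index". Four kinds of accuracy measure follow: likelihood ratios, predictive values, sensitivity and specificity. AUC is not named.

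On numbers, section 2.1.1 says: "Four cohorts of 40 individuals each will be recruited: heatstroke patients, sepsis patients, patients undergoing CPB, and healthy controls". Section 2.3 says: "we aim to enroll at least 40 subjects in each of the four cohorts". It gives no power calculation: "We did not calculate minimal sample size to achieve a given statistical power because this is an exploratory study". By section 2.2, prognosis concerns the heatstroke cohort only, with 30-day death from any cause as primary endpoint. The Introduction says that "mortality rates of heatstroke patients can be as high as 30–60"%. The candidate subsets come from automated clustering of the antibody panels in section 2.4.3, and no count of candidates is given.

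**The concern.** A cut-off that maximises sensitivity plus specificity in a sample fits the chance features of that sample as well as the real separation. If accuracy is then read off at that cut-off in the same patients, it is better on average than new patients would show. The bias grows as the smaller outcome group shrinks, so prognosis, which turns on the number of deaths among 40 patients, is more exposed than diagnosis.

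Finding diagnostic and prognostic biomarkers is the aim stated in the Introduction and section 2.2, and these accuracy figures are the evidence for it. A reader who takes them at face value would credit a marker with more discrimination than it has.

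**Working it through.** The plan states no target AUC, power or expected accuracy, so there is no figure of its own to reproduce. The check asks how far apparent accuracy exceeds true accuracy at the plan's sample sizes.

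**Inputs**
- Diagnosis: 40 v 40 for each pair of cohorts (sections 2.1.1 and 2.3).
- Prognosis: 40 heatstroke patients. From the Introduction, 40 × 0.30 = 12 deaths (28 survivors) up to 40 × 0.60 = 24 deaths (16 survivors). The range is introduced as an upper level, so fewer deaths are possible.
- Assumed: normally distributed markers with equal variance in both groups; true AUC 0.70 for an informative marker and 0.50 for noise; 50 candidates where selection is considered.

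**Formulae**
- Youden index J = sensitivity + specificity − 1.
- Separation of group means in SD units: δ = √2 × Φ⁻¹(AUC). For AUC 0.70, δ = 1.414 × 0.524 = 0.742.
- Best J attainable with the ideal cut-off: 2Φ(δ/2) − 1 = 2 × 0.6446 − 1 = 0.289.
- True J at an estimated cut-off t: Φ(t) − Φ(t − δ).

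**Step 1: cut-off effect alone (one marker, true AUC 0.70, no selection)**

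| Groups | Apparent sens./spec. | True sens./spec. | Apparent J | True J | Excess |
|---|---|---|---|---|---|
| 40 v 40 | 0.67/0.70 | 0.61/0.65 | 0.37 | 0.27 | 0.10 |
| 12 v 28 | 0.73/0.70 | 0.60/0.66 | 0.43 | 0.25–0.26 | 0.17–0.18 |
| 24 v 16 | 0.68/0.73 | 0.61/0.65 | 0.41 | 0.26 | 0.16 |

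Excesses are taken before rounding. Independent runs agree to within about 0.01. Mean apparent AUC is 0.70 throughout, so the Youden step leaves AUC unbiased.

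The bias carries into the derived measures. The positive likelihood ratio, sensitivity/(1 − specificity), from the unrounded averages is 0.672/0.302 = 2.2 apparent against 0.614/0.347 = 1.8 true at 40 v 40. At 12 v 28 it is 0.730/0.303 = 2.4 against 0.597/0.342 = 1.7.

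Sensitivity to inputs: with true AUC 0.80, J is 0.52 v 0.43 at 40 v 40 and 0.56 v 0.41 at 12 v 28. With an assumed 4 deaths and true AUC 0.70, J is 0.50 v 0.24.

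**Step 2: if subsets are also chosen for differing in the same patients**

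A noise marker that happens to reach p < 0.05 shows a mean AUC (taken in whichever direction exceeds 0.5) of 0.65 at 40 v 40, 0.73 at 12 v 28 and 0.72 at 24 v 16. The truth is 0.50. With 50 independent noise markers, the chance that at least one passes is 1 − 0.95⁵⁰ = 0.92.

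**Step 3: worst-case illustration (best of 50 independent noise markers)**

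| Groups | Apparent AUC | Apparent J |
|---|---|---|
| 40 v 40 | 0.66 | 0.34 |
| 12 v 28 | 0.75 | 0.52 |

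Here AUC and J are each maximised over the 50 markers. If J is read from the marker with the best AUC, it is 0.32 and about 0.50. With an assumed correlation of 0.7 between all markers, that marker's AUC and J fall to 0.63 and 0.28 at 40 v 40, and to 0.70 and 0.43 at 12 v 28. True J is 0 throughout.

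**The case against.** The strongest reply is that the study calls itself exploratory, makes no power claim and uses a common way to choose a cut-off. That affects how firmly the results should be read. It does not take the bias out of the numbers reported.

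Three stronger readings are tempting, and the document does not support them.
- **That the plan screens every subset and carries only significant ones into the ROC analysis.** Section 2.5 only refers back to the subsets tested; it states no filter and no choice of the best. If every subset examined is reported, the AUCs are not inflated on average. Steps 2 and 3 are therefore conditional; step 1 is not.
- **That no internal validation is intended.** Only a condensed article is at hand, and resampling details may stand in a fuller document. The point rests on the threshold rule that the article does fix and on the measures it attaches to that rule.
- **That worthless markers will look good throughout.** For diagnosis, even the best of 50 noise markers reaches only about 0.66 sensitivity and 0.66 specificity, which few would call good. The prognostic figures come closer, but they need many independent noise markers and few deaths.

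It is also fair to say that correction will not make prognosis precise. With 12 deaths, a sensitivity of 0.80 has a 95% half-width of 1.96 × √(0.8 × 0.2/12) = 0.23.

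**Conclusion.** The point holds for accuracy measured at the data-derived cut-off. Its direction is certain and needs no assumption about the number of markers. For one marker of true AUC 0.70, the Youden index is overstated by about 0.10 in a 40 v 40 diagnostic comparison and by about 0.17 at 12 deaths v 28 survivors. These sizes rest on normal markers with equal variance and on the mortality range in the Introduction; fewer deaths make the excess larger.

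Inflation of AUC is conditional. It follows only if the subsets reported are picked because they differed in the same patients. Its size then depends on how many candidates there are and how correlated they are, and the document gives neither. The 50-marker figures are a worst-case illustration and not a forecast for this study.

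**What to change.** In section 2.5, state that sensitivity, specificity and AUC will be reported after correction for optimism, with 95% confidence intervals. Use the bootstrap or repeated cross-validation, and repeat any marker selection and the Youden cut-off inside every resample. Correcting the cut-off while keeping a marker chosen on the full data would leave the selection bias in place. Derive likelihood ratios and predictive values from the corrected sensitivity and specificity. Label uncorrected figures as apparent, and base conclusions on the corrected ones. State also whether every subset examined will be reported or only those that differed.

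The cost is a paragraph of text and a short script outside Prism, with no extra patients or samples. The reported accuracy will be less favourable. The prognostic intervals will be wide because deaths are few, and the report should say so.
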